**Figure 3 F3:**
[figure not shown]
Randomization with intervention.

After the registration, the palm will recognize the oncologist (scroll bar) and automatically provide the software for the control or the E-MO*S*AIC arm, respectively. After synchronization the unique patient number (UPN) will be updated immediately, with maximal 12 patients per oncologist only 12 patient-UPNs will be possible.

This trial design was chosen in order to minimise contamination. Several patients allocated to the same physicians can hardly be considered independent. In particular, a physician familiar to the LoMoS intervention would probably treat his patients in a similar way, even if they were randomized to different interventions. To prevent this contamination, physicians are chosen as clusters [29]. Cluster randomisation is a standard approach to evaluate both process outcomes and patient outcomes, and is considered especially relevant if the intervention is on physician level and outcomes are patient reported [30].

### Randomization procedure and patient registration

Participating physicians are randomly allocated to the intervention or control arm. Hence, all eligible patients allocated to a physician will be under the same intervention.

Before randomization, the center needs to be activated and the initiation visit has taken place. Each physician has to be informed about the study procedures and has to sign informed consent prior to his randomization. There will be no specific training on symptom management, because the E-MOSAIC intervention in this study includes simply the monitoring sheet. Patient registration is only possible for randomized physicians. Patients give informed consent prior to any protocol-specific procedure.

### Data collection procedures

Patients are seen in all clinics first by oncology nurses who perform the baseline visit, educate patients about the use of the palm, ask patients about oncologist’ interventions in the previous week, and perform at weeks 3 and 6 the outcome assessments.

At baseline, weeks 3 and 6, the cognitive status of patients is assessed.

Since mild cognitive impairment is well reported to be underestimated but influencing patients’ ability to express subjective experience of well-being and symptoms, cognitive function will be monitored throughout the study (Figure 4).

**Figure 4 F4:**
[figure not shown]
Study flow with visits and forms.

To screen for patients with cognitive impairment at baseline, the Mini-Cog, a brief cognitive screening test, will be used. The Mini-Cog and the Mini-Mental Status Examination applied post-hoc to an existing population revealed similar sensitivity (76% vs. 79%) and specificity (89% vs. 88%) for dementia. Therefore, the Mini-Cog test is feasible in settings where time is short, training of personnel is not possible and/or language barriers exist [31].

### Objectives and endpoints

The objective of the study was to evaluate the effects of the intervention using E-MO*S*AIC palm and real-time longitudinal monitoring sheet (LoMoS) in patients receiving anticancer treatment for advanced cancer in palliative intention.

Change in Global Quality of Life (G-QoL) is the primary endpoint. The difference in G-QoL between baseline and after last study visit is measured. The change in QoL will be assessed using the EORTC-QLQ-C30 composed of both multi-item scales and single item measures. Patient will complete the EORTC-QlQ-C30 at baseline and at week 3 and 6 after consultation. G-QoL is the composite score of questions 29 and 30. This instrument is well validated, frequently used and provides a large data base of normative data [32].

Secondary endpoints are the number of patients having a G-QoL response, physician-patient communication, symptoms and syndromes and symptom management performance.

Responders are defined as having a better rated G-QoL assessment after last study visit compared to baseline of more than half of standard deviation of the G-QoL changes of whole study population.

Patients’ estimation of the patient-physician communication will be assessed by a physician compassion rating and general physician attribute rating scales (27).

The rating of the physician compassion uses a semantic differential format including five pairs of physician characteristics. The characteristics are warm-cold, pleasant-unpleasant, compassionate-distant, sensitive-insensitive, caring-uncaring. The two attributes are the left and right anchor of a 100 mm line with each item ranging from 0–100. This scale has been reported to be internally consistent (Cronbach’s alpha coefficient, .92) in cancer survivors and non-cancer patients. A composite score can be calculated (ranging from 0 to 500) [33].

For general physician attributes five other pairs of statements in a semantic differential format will be used: 1) wants best for patients, 2) patient involvement in decision-making, 3) encourage patients’ questions, 4) acknowledging patients’ emotions, and 5) caring for patients. Patients will be asked to rate each of the questions in a scale of 0 (worst) to 100 (best).

Physician’s estimation of the patient-physician communication will be assessed by a questionnaire comprising 7 ad-hoc statements covering satisfaction with amount and clarity of provided information, estimation of patients’ comprehension of information and satisfaction of patient involvement in decision making process. This evaluation tool was developed for the SAKK communication trial [34].

Symptoms and Syndromes from the E-MOSAIC software between baseline and after last study visit will be evaluated. Symptom Distress Score, the summation of the nine ESAS items is used as in the original publication [35]. All ESAS symptoms are individually investigated, to test the hypothesis, that the E-MOSAIC intervention may influence only specific symptoms (e.g., only anxiety and depression, but not pain, or vice versa). As syndromes, pre-defined selected items, the KPS, weight and weight loss, nutritional intake, and use of medical interventions for symptoms (e.g. MEDD) are compared. Several of these items have been conceptualized as clinical benefit criteria.

Number of visits with a symptom load above defined threshold for 5 symptoms without immediate intervention and all interventions performed by the oncologist to alleviate multidimensional suffering of patients and family members will be calculated and oncologists’ routine work will be collected. From the visits all routinely available information describing physician’ diagnostic or therapeutic interventions are collected: visit flow sheets, visit notes and reports, lab sheets, order sheets, and nurses’ notes.

To capture interventions made by the oncologist for any of the multidimensional (symptom) problems, which the patient recalls one week later, the patient will be asked before each visit: “did your doctor prescribe or initiated treatments or interventions to relieve your physical, emotional, or social distress/burden, and if so, please briefly mention them.”

To compare the number of interventions made for key symptoms above defined thresholds. For this study is chosen:

• visits (#) with pain > = 6/10 and no immediate change of analgesics

• visits (#) with fatigue > = 9/10 and no immediate diagnostic or therapeutic intervention

• visits (#) with anorexia > = 9/10 and no immediate diagnostic or therapeutic intervention

• visits (#) with depression > = 6/10 and no immediate diagnostic or therapeutic intervention

• visits (#) with shortness of breath > = 6/10 and no immediate diagnostic or therapeutic intervention

A medical fellow, having at least 2 years clinical experience, who is blinded to the randomisation (the UPI system does not allow to identify institutions nor individual oncologists), will analyse for each patient the visit description and patient recalled interventions of last visit to search for such interventions.

From the visits the following variables are collected: medications and changes, diagnostic interventions, delegated interdisciplinary interventions, and patient perceived interventions.

Additional research questions investigate factors influencing change in G-QoL, tumor response (CR, PR, SD or PD), tumor type, predominant symptom, anxiety, complexity, education and hospitalization. A predominant symptom is defined as the symptom with the highest ranking and all other symptoms are > =2 / 10 lower ranked. Complexity is defined as > =3 symptoms with > =6/10, with the exception of fatigue and anorexia (threshold > =9/10).

To explore patients’ subjective adaptation to illness and burden of treatment two linear analogue self-assessment (LASA) indicators are included, assessing perceived adjustment to chronic illness (PACIS); [34] (‘no effort at all’ – ‘a great deal of effort) and overall treatment burden (‘not at all’ – ’severely’). The indicator for PACIS was confirmed to be responsive to cytotoxic side-effects, mental distress, and psychosocial dysfunction in patients with early breast cancer [36]. It is suitable to describe patients’ adaptation over time. The instruments are validated [37]. The indicator for overall treatment burden has been validated regarding side-effects of antiemetic and cytotoxic therapy [38].

As indicator for decision-making preferences, the difference in number of mismatched decision-making preferences between week 3 and 6 will be compared between the two arms.

Patients’ preferences for involvement in decision making will be assessed by a measure adapted from previous studies [39]. The patient chooses from among five categories ranging from ‘the doctor should make the decision using all that he/she knows about the treatment’ to ‘I should make the decision using all that I know and learn about the treatment’. In addition the physician is asked to choose from among the same five categories how he/she estimates the patients’ preferences.

A mismatch is defined as follows: the patient ranks #1 or #2 and the physician #4 or #5 or vice versa. For neutral patients or physicians no mismatch is possible per definition.

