### Sample size calculation

Sample sizes are calculated for an inequality test for two means of change in QoL in a cluster randomized design using the software package NCSS 2004 - PASS 2002, according to the formulation of Donner and Klar, assuming a two-sided significance level of 0.05, and a statistical power of 0.8 [40]. Further assumptions on design parameters are an overall variance (s2) of 400, an intracluster correlation coefficient (ICC, estimated by the ratio of between-cluster variation to overall variance) of 0.05 , an effect size (between-arm difference in G-QoL to be detected) of 10, and the cluster size (the number of evaluable patients per physician) [40]. For the cluster size several options are considered, but it is expected to stop the trial at a cluster size of 8 with 12 physicians per arm, yielding a total sample size of 192 evaluable patients.

Since the initial estimate of the ICC might not be appropriate, an interim analysis to adjust the sample size as suggested in Lake et al. is foreseen [41]. Once data for the first 100 patients are available, estimates of within-cluster variation and between-cluster variation are obtained. If the resulting ICC has to be at least 1.5 times larger than the value taken for the initial sample size estimation, then the sample size would be adjusted using the new estimate of ICC, without alteration on other design parameters. The feasibility of patient accrual is evaluated at the same time. The recommended cluster size might be adjusted accordingly.

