### Data analysis

Due to the cluster structure, comparisons of different outcomes between treatment arms will be analyzed by mixed models. For endpoints with continuous values, linear mixed model may be applied. For endpoints with categorical or binary values, nonlinear mixed model or generalized estimating equations may be applied.

The data will be stored and analyzed at the SAKK Coordinating Center using SAS software, Version 9.2 of the SAS System for Windows (SAS Institute Inc., Cary, NC, USA) and the open source R statistical software package (http://www.r-project.org/). All statistical tests will be done two-sided at a significance level of 0.05. P-values will be corrected for multiple testing where appropriate.

Descriptive statistics will be done by median and range for continuous variables. Categorical data will be reported using absolute and relative frequencies.

For the *primary endpoint*, selected influential variables (education, tumor type, predominant symptom, anxiety, complexity, hospitalisations) and the baseline G-QoL value will be included in the analysis model as covariates. For the primary analysis, only evaluable patients will be used. As a sensitivity analysis, non-evaluable patients will be included if possible. For instance, the difference between baseline and 3 weeks will be analyzed including patients who are evaluable at week 3 but non-evaluable at week 6.

Several pre-defined subgroup analyses are foreseen: The difference in G-QoL will be compared between both arms in sub-groups of patients having

a) a tumor size response (SD, PR, CR) or not (PD),

b) basic education or additional education

c) one of the main tumor types defined as composing > = 20% of the evaluable study patients.

d) a predominant symptom, if composing > = 20% of the evaluable study patients (expected based on symptom epidemiology data: pain, anorexia and/or fatigue [both predominant vs. other symptoms or alone vs. other symptoms], anxiety and/or depression [both predominant vs. other symptoms or alone vs. other symptoms], nausea, shortness of breath).

e) anxiety <6/10 or > =6/10

f) complexity less than 3 symptoms above threshold vs. > = 3 symptoms above threshold (fatigue and anorexia > =9/10, other symptoms > =6/10).

All subgroup analyses will include baseline G-QoL as covariate.

The study population will be described separately by institution (study center)-, oncologist-, and patient-related factors.

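### Separate tests of each ESAS symptom do not test whether the intervention acts on some symptoms only; that needs a comparison of effects between symptoms

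*Protocol article*

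**What the plan says.** Objectives and endpoints lists symptoms and syndromes among the secondary endpoints. It first names a total score: "Symptom Distress Score, the summation of the nine ESAS items is used as in the original publication". It then turns to the single items: "All ESAS symptoms are individually investigated, to test the hypothesis, that the E-MOSAIC intervention may influence only specific symptoms", with the example "e.g., only anxiety and depression, but not pain, or vice versa".

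Data analysis supplies the method for all endpoints: "comparisons of different outcomes between treatment arms will be analyzed by mixed models", and "All statistical tests will be done two-sided at a significance level of 0.05". On multiplicity it says only "P-values will be corrected for multiple testing where appropriate".

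The article mentions no arm-by-symptom interaction, no test of heterogeneity across symptoms, and no margin by which an effect on pain could be called absent. It also states no rule for turning nine item results into a conclusion about specificity.

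**The concern.** A claim that anxiety and depression respond but pain does not is a claim about a difference between effects. It is supported only by evidence that the effects differ. The item-by-item comparison instead asks, nine times, whether one effect is zero. A significant result for anxiety beside a non-significant one for pain shows neither that the two effects differ nor that pain is unaffected.

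The trial is sized for one endpoint at 80% power, so single symptoms with modest true effects will often miss significance by chance. If the nine results are read against each other, the report could describe a symptom-specific mechanism that does not exist and tell readers that monitoring does not help a symptom such as pain.

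**Working it through.** **Inputs from the article.** Sample size calculation: "assuming a two-sided significance level of 0.05, and a statistical power of 0.8"; "an overall variance (s2) of 400", so SD = √400 = 20; ICC 0.05; difference to detect 10 points, so 10/20 = 0.5 SD; 12 physicians per arm with 8 patients each, 192 in all. Interim analysis: revised to 20 clusters per arm with 4 patients each, 160 in all, plus 5% to give 168.

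**Assumptions not in the article.** Symptom effects of 0.2 to 0.6 SD, identical on all nine items; correlation between symptoms 0.3, 0.5 or 0.7; the same ICC of 0.05 for every symptom; equal cluster sizes.

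**Step 1: reproduce the plan's own sample size.** With k clusters per arm of m patients, the standard error of the arm difference in SD units is √(2[1 + (m − 1) × ICC]/(mk)). Power follows from the noncentral t distribution with 2(k − 1) degrees of freedom.

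- m = 8, k = 12: √(2 × 1.35/96) = 0.1677; noncentrality 0.5/0.1677 = 2.98; 22 df; power 81.3%.
- m = 4, k = 20: √(2 × 1.15/80) = 0.1696; noncentrality 0.5/0.1696 = 2.95; 38 df; power 82.0%.

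One cluster fewer per arm falls below 80% in both cases (77.5% and 79.9%), so both stated designs are reproduced.

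**Step 2: power for one symptom (m = 4, k = 20).** The same formula gives 21%, 41%, 63%, 82% and 93% at 0.2, 0.3, 0.4, 0.5 and 0.6 SD. A single unadjusted test therefore misses a true effect in 59%, 37% and 18% of trials at 0.3, 0.4 and 0.5 SD.

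**Step 3: how nine tests split when the effect is equal on all nine.** Trials were simulated with a two-sided t-test on cluster means for each symptom. A split means at least one but not all nine tests significant. The joint test is Hotelling's T² on the 8 between-symptom contrasts. At correlation 0.5:

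| Equal effect | Split, unadjusted | Split, Bonferroni | Anxiety and depression significant, pain not (unadjusted) | Joint test rejects |
|---|---|---|---|---|
| 0.2 SD | 62% | 24% | 4% | 5% |
| 0.3 SD | 79% | 49% | 7% | 5% |
| 0.4 SD | 77% | 73% | 9% | 5% |
| 0.5 SD | 56% | 82% | 7% | 5% |
| 0.6 SD | 30% | 71% | 4% | 5% |

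Over correlations 0.3 to 0.7 and effects 0.3 to 0.5 SD, the unadjusted split ranges from about 44% to 90%. A separate calculation with normal test statistics at 168 patients gives 63%, 80%, 73%, 49% and 23% at correlation 0.5, which agrees broadly.

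**Step 4: does the joint test detect real specificity?** When only anxiety and depression improve, by 0.5 SD each, it rejects in 81%, 93% and 99.6% of trials at correlations 0.3, 0.5 and 0.7.

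**Step 5: does multiplicity correction help?** At correlation 0.5, Bonferroni lowers the split at 0.2 to 0.4 SD and raises it at 0.5 and 0.6 SD. Across the table it stays between 24% and 82%, well above 5%. Correction controls false claims of an effect; it does not turn the nine tests into a test of equality.

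**The case against.** The strongest reply is that the article never says a split will be read as specificity. It is a condensed report, and an analysis plan not shown here could hold an interaction test. The sentence also follows directly on the summed score, so it may mean only that single items are examined because an effect confined to a few symptoms could be diluted in the total. For that purpose, separate arm differences are the right quantity.

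This stands in part. The reading rule is an inference, and the simulated figures hold only if that rule is applied. But the article itself presents the item-by-item investigation as the test of the specificity hypothesis, and its example includes a symptom that is not influenced. A method stated for a hypothesis it cannot test is more than omitted detail.

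Three stronger readings are tempting, and the documents do not support them.

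- *Equal effects would be called specific in most trials, or nearly always.* This depends on effect sizes and correlations that the article does not give. At the planning effect of 0.5 SD and correlation 0.5 it is near a coin toss (56%, or 49% in the second calculation), and at 0.6 SD it is about 30%.
- *The article's own example would often arise by chance.* Anxiety and depression both significant with pain not occurs in about 7% to 9% of trials at 0.3 to 0.5 SD and correlation 0.5. Those two significant and no other symptom occurs in under 1%.
- *Multiplicity correction makes matters worse.* Step 5 shows that this depends on the effect size.

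The joint test has limits too. The 5% rate comes from equal clusters and equal variances; the mixed model recommended below was not itself simulated, and Interim analysis reports many clusters with one or two patients or none. Eligibility requires only one symptom of at least 3/10, so other items may start near zero. Under assumed baselines with a floor at 0 and an equal underlying shift, a joint test on raw points rejected in 8% to 42% of trials, against 5% to 8% on the SD scale. The choice of scale is therefore a real one.

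**Conclusion.** The concern holds in a limited form. The stated item-by-item comparisons test no effect on each symptom, not equal effects across symptoms, so they cannot test the hypothesis attached to them. If, and only if, a mix of significant and non-significant items were taken as specificity, a uniform effect would look specific in about 44% to 90% of trials at 0.3 to 0.5 SD and correlations 0.3 to 0.7, against about 5% for a joint test. These figures rest on 20 clusters of 4 per arm, ICC 0.05, and assumed symptom effects and correlations. The article does not say that the results will be read in this way. The matter should be corrected, but it concerns one secondary analysis and leaves the G-QoL conclusion untouched.

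**What to change.** Base any conclusion about symptom specificity on an arm-by-symptom interaction in one joint mixed model of the nine ESAS changes, with patient and physician random effects and baseline values. One pre-stated contrast, for example anxiety and depression against the other symptoms, could serve instead or be added. State the scale on which effects count as equal before the data are seen; standardised effects are preferable because of possible floor effects. Report the nine individual arm differences with 95% confidence intervals as description, and do not infer absence of an effect on pain from p > 0.05. If no joint model is wanted, call the item results descriptive and drop the statement that they test the specificity hypothesis.

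The cost is one extra model on data already collected, with no added patients. The drawbacks are the scale choice, which can change the interaction result, and that an omnibus interaction test does not itself show which symptom is spared.

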**Methods:**

In this prospective multicentre cluster randomized phase-III trial patients with any incurable solid tumor and having defined cancer related symptoms, who receive new outpatient chemotherapy in palliative intention (expected tumor-size response rate ≤20%) are eligible. Immediately before the weekly visit to oncologists, all patients complete with nurse assistance the E-MO*S*AIC Assessment: Edmonton Symptom Assessment Scale, ≤3 additional symptoms, estimated nutritional intake, body weight, Karnofsky and medications for pain and cachexia. Experienced oncologists will be randomized to receive the LoMoS or not. To minimize contamination, LoMoS are removed from the medical charts after visits. Primary endpoint is the difference in global quality of life (items 29 & 30 of EORTC-QlQ-C30) between baseline and last study visit at week 6, with a 10 point between-arm difference considered to be clinically relevant. 20 clusters (=oncologists) per treatment arm with 4–8 patients each are aimed for to achieve a significance level of 5% and a power of 80% in a mixed model approach. Selected co- variables are included in the model for adjustment. Secondary endpoints include patient-perceived patient-physician communication symptom burden over time, and oncologists’ symptom management performance (predefined thresholds of symptoms compared to oncologists’ pharmacological, diagnostic or counselling actions [structured chart review]).

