**Figure 1 F1:**
[figure not shown]
Screenshot from Palm as illustration.

The palm-based assessment consists of three elements (see screenshots in the Appendix), which are filled out by the patient (element P) and the study personnel (elements G [weight] and M [medication]).

Element P Visual-Analogue Scales (VAS) of

1. Nine frequent symptoms from ESAS (pain, fatigue, drowsiness, nausea, anxiety, depression, shortness of breath, loss of appetite, overall well-being);

For E-MOSAIC the single symptoms of the original ESAS were translated in German, French and Italian language in an informal back- and forward process, and validated preliminarily. ESAS is measured by palm in all patients.

2. Up to three optional symptoms;

3. Patients’ estimated nutritional intake.

Element G:

1. Body weight;

2. Karnofsky Performance Status;

3. Weight loss and body height (Body Mass Index calculated automatically).

Element M: pre-defined, simplified list for actual medication for:

1. Pain syndromes, including assessment of MEDD (Morphin Equivalent [oral] Daily Dose);

2. Fatigue syndromes (Methylphenidate, Erythropoietin, transfusions);

3. Anorexia/cachexia syndromes, and for edema (to control for weight changes).

After completion of the assessments the palm is put back to the docking station and the data are transferred within a few seconds from the docking station to the local computer.

The source-code of the E-MOSAIC software is copy-protected. The software is study-specific, but may be used for other purposes.

Longitudinal Monitoring Sheet LoMoS which is printed immediately and put in the patient file for the physicians’ visit by the nurse (Figure 2).

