A large body of evidence builds the foundation for practice guidelines in symptom management of advanced cancer patients, allowing agreed-on classifications of various types of symptom control interventions and thresholds of symptom expression. However, as in other medical disciplines, variability in symptom management practice is common, driving academic exchanges including research and scholar literature. Therefore, in this study, no practice guidelines are provided nor explored.

The reactions to symptoms may therefore vary between physicians as well as the documentation of the interventions.

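### Symptom management performance: the stated reason for the reviewer's blind covers identity but not note content, and fuller notes alone could lower the no-intervention count

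*Protocol article*

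**What the plan says.** Under Objectives and endpoints, the Protocol article defines symptom management performance through counts of visits at which one of five symptoms passes a set level and nothing is done. An example is "visits (#) with depression > = 6/10 and no immediate diagnostic or therapeutic intervention". The information collected comprises "visit flow sheets, visit notes and reports, lab sheets, order sheets, and nurses’ notes". The medical fellow "will analyse for each patient the visit description and patient recalled interventions of last visit to search for such interventions", and is described as someone "who is blinded to the randomisation (the UPI system does not allow to identify institutions nor individual oncologists").

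Three other places bear on this:

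- Development of intervention tool: in the intervention arm the printed sheet is "put in the patient file for the physicians’ visit by the nurse". The same section says that "ESAS is measured by palm in all patients".
- Abstract, Methods: "To minimize contamination, LoMoS are removed from the medical charts after visits".
- Limitations: "The reactions to symptoms may therefore vary between physicians as well as the documentation of the interventions".

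Under Data collection procedures, oncology nurses are the ones who ask patients what the oncologist did in the week before.

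**The concern.** There are two separate problems, and curing one does not cure the other.

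**Masking.** Coding the physician stops the fellow from looking up the allocation. It does nothing to the text the fellow reads. In the LoMoS arm that text is written by an oncologist who has just been given the sheet and by nurses who handled it. A remark in a note that refers to the sheet would disclose the arm. Whether an action counts as an immediate intervention involves some judgement, so knowing the arm could tilt the scoring.

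**Documentation.** No intervention is in practice no intervention found. A sheet listing symptom scores may lead the oncologist to write more about symptoms and about what was done, whether or not more was done. The Limitations section accepts that documentation differs between physicians, but not that the intervention may shift it by arm.

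At stake is the reading of the trial's direct measure of physician behaviour. A lower count in the LoMoS arm could be reported as better symptom management when part or all of it is better record-keeping.

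**Working it through.** The document gives no figure on this point, so there is nothing to reproduce. The check sets the passages side by side and then uses an illustration with assumed rates.

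**1. Does the stated reason support the stated blind?** The claim is blinding to randomisation. The reason is that physician and institution cannot be identified. Physicians are the randomised units, so hiding them is necessary, but it is sufficient only if the records carry no other sign of the arm. The article gives no other measure at that point. Removal of the sheet, described in the Abstract, takes away the most direct sign. Its stated purpose is to limit contamination, and it leaves untouched anything written about the sheet.

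**2. Which inputs to the endpoint can differ by arm?**
- Threshold status: no documentation route, because the scores come from the palm in all patients.
- Whether an action is found: yes, because this depends on what staff wrote and on recall gathered by nurses.

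**3. Size of the documentation effect.** Let p be the true share of above-threshold visits with an action, and s the probability that an action is documented or recalled and then found. Neither is in the document; both are assumptions.

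- Scored no-intervention share = 1 − p × s
- Spurious difference when p is equal in both arms = p × (s_LoMoS − s_control)

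With capture of 80% in control and 90% in LoMoS records:
- p = 0.5: 1 − 0.5 × 0.8 = 0.60 against 1 − 0.5 × 0.9 = 0.55, a difference of 5 points
- p = 0.6: 1 − 0.6 × 0.8 = 0.52 against 1 − 0.6 × 0.9 = 0.46, a difference of 6 points

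Range of the spurious difference, in percentage points:

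| Gain in capture | p = 0.3 | p = 0.5 | p = 0.7 |
|---|---|---|---|
| 0 | 0 | 0 | 0 |
| 5 points | 1.5 | 2.5 | 3.5 |
| 10 points | 3 | 5 | 7 |
| 20 points | 6 | 10 | 14 |

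If capture were lower in the LoMoS arm, the sign would reverse.

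**4. Can the planned count tell documentation from action?** Not by itself. Take a control arm at 60% (p = 0.5, s = 0.8). A LoMoS arm at 55% arises equally from p = 0.5 with s = 0.9 (found: 0.5 × 0.9 = 0.45) and from p = 0.5625 with s = 0.8 (found: 0.5625 × 0.8 = 0.45). Only a source whose capture depends less on note-writing can separate them. If capture is equal in both arms, the first case gives p × (s − s) = 0, while a real increase in action still shows.

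**The case against.** The case on the other side is substantial.

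- **The article is a condensed account.** How records are copied, masked and coded may be set out in the full protocol or a review manual that is not shown. This stands: the absence of a masking procedure from the article is not an error. The mismatch between the stated reason and the stated blind is in the text, however, and remains.
- **The sheet is removed from the chart.** This also stands. A reader might infer that the blind rests on coded identifiers alone, or that the fellow is in fact unblinded. The document supports neither. Disclosure through wording in notes is possible, not shown.
- **Symptom scores and doses in a note do not mark the arm.** A reader might think that they do. But ESAS is taken by palm in every patient, and the Abstract has pain and cachexia medications assessed in all patients, so such values can appear in either arm. Only an explicit reference to the monitoring sheet is specific.
- **Scoring does not rest on free text alone.** Order and lab sheets are collected, the pain criterion concerns a change of analgesics that orders can show, and patient recall does not depend on the oncologist's notes. This reduces the documentation effect. It does not remove it, because the planned count pools all sources.
- **Variable documentation is already a named limitation.** That covers variation between physicians, not a shift caused by the intervention.
- **Blacking-out could itself reveal the arm.** Site staff who know the arm would do it, and the marks would fall mainly on intervention charts. This stands, and is why redaction is not the main remedy.

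**Conclusion.** The point holds in a limited form. The reason given for the blind protects against identifying the physician or institution, and does not reach the content of the notes. Independently of blinding, the no-intervention count is open to a difference in documentation between arms that the article does not consider.

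The size cannot be derived from the document. Under the assumed rates the spurious difference runs from 0, when capture is equal, to 14 percentage points at p = 0.7 with a 20-point gain in capture; 5 points is a middle case. The direction favours LoMoS only on the assumption that the sheet makes notes fuller. The masking route is not quantified.

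The text does not support concluding that the endpoint is invalid. The issue is confined to one secondary endpoint group. The primary endpoint is patient-reported global quality of life, and neither it nor the sample size is touched. The change is worth making because it is cheap and decides whether a benefit on this endpoint can be read as changed behaviour.

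**What to change.** Amend the description of the chart review under Objectives and endpoints:

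1. State that the fellow codes actions for every visit without seeing the ESAS scores, and that a program then applies the thresholds. The article does not say whether the fellow sees the scores.
2. Add a sensitivity scoring restricted to order sheets and medication records. Order sheets are already collected, and medications and their changes are among the listed variables. If a benefit appears only in the scoring that includes notes and recall, interpret it cautiously.
3. If explicit references to the monitoring sheet are masked, use the same procedure in both arms so that the masking does not signal the arm. If they are not masked, describe the reviewer as masked to physician and institution identity.

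**Cost.** No new data collection, but some extra coding and one extra table. If the fellow would otherwise read only above-threshold visits, item 1 adds the rest: at most about 264 × 6 = 1,584 visit records, taking the 264 patients given under Interim analysis and six weekly visits each. The restricted scoring misses counselling that is never ordered, so it belongs beside the planned scoring and should not replace it. Masking under item 3 would take clerical time at the centres and is optional.
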